***Allocation, randomization, and blinding of study treatment (intervention):***

***Randomization method:*** A 2 X 2 variable blocked randomization code (ranging between 4 and 8 per block), with stratification by study site and first versus previous episode of wheeze, will be produced by the Drug Development and Innovation Centre at the university of Alberta (DDIC) using random-number generating software. DDIC will produce the study packages, complete the block randomization, and number the bottles. The blinded and numbered study drug packages, in addition to the master code will be available to both study sites if de-blinding is required. Stratification by ‘history of wheeze’ will allow us to track the number enrolled into each sub-group, and ensure we achieve our targeted sample size for each one. We have included children with both first and prior episode of wheeze and powered our study to perform a sub-group analysis for these two groups. Macrolide therapy has been shown to be effective in both bronchiolitis and asthma; incorporating both populations into this study design may provide important insights into how these populations of patients might differ.

Children will be defined as first-time wheezer if they have never had symptoms of wheeze prior to this episode, the symptoms of wheeze have been occurring for < 1 month with no period without resolution of symptoms for greater than 1 week during that 1 month period. Resolutions of symptoms include absence of all respiratory symptoms including wheeze, cough, respiratory distress, and shortness of breath. Some illustrative examples: If the patient has had symptoms for greater than 1 month- these children would be considered a repeat wheezer. If the child has had symptoms of wheezing for 1 month but had a 1 week period without respiratory symptoms in that one month, and we are seeing them after the 1 week resolution period, these children would be also be considered a repeat wheezer. IF the child has had wheezing symptoms for 1 month but was never symptoms free for more than 1 week continuously, this child would be considered a first-time wheezer.

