***Blinding of azithromycin:*** The pharmacy at each site will prepare two boxes (one for children enrolled with ‘first episode of wheeze’ and the other for those with ‘prior episode of wheeze’) of sequential patient packets containing the study drug in sealed, opaque, numbered bags. Each bag will contain 2 X 10 cc syringes, and either study drug or placebo that will be indistinguishable by appearance, smell, and taste. The two boxes of patient packets (first-time wheezing patient, previous wheezing patient box) will be kept in a locked and secure room in the ED for use as patients are enrolled. The research assistant who assigns the intervention will be unaware of the next group assignment as study drugs will be packaged identically and identified only by a sequential study number.

***Randomization code access:*** The Research team from both sites will have access to the master randomization code until patient enrolment is completed and all decisions regarding statistical analyses are finalized.

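### The first-time-wheezer rule contradicts its own worked examples and its one-month and one-week limits conflict, so one child can fit either randomisation stratum

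*Protocol*

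**What the plan says.** Protocol section 6, Randomization method, stratifies randomisation by site and by first or previous episode of wheeze. A first-time wheezer must meet three conditions:

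- no wheeze before the present episode;
- a limit on duration, namely "the symptoms of wheeze have been occurring for < 1 month";
- a further condition on how the illness has run, namely "with no period without resolution of symptoms for greater than 1 week during that 1 month period".

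The next sentence defines resolution: "Resolutions of symptoms include absence of all respiratory symptoms including wheeze, cough, respiratory distress, and shortness of breath".

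Three worked examples follow.

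- Example 1: "If the patient has had symptoms for greater than 1 month- these children would be considered a repeat wheezer".
- Example 2: a child with wheeze for one month who "had a 1 week period without respiratory symptoms in that one month", and who is seen after that gap, is a repeat wheezer.
- Example 3: "IF the child has had wheezing symptoms for 1 month but was never symptoms free for more than 1 week continuously", the child is a first-time wheezer.

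The classification is used in four places. It is a stratification factor. Under Blinding of azithromycin it decides which of two boxes supplies the packet, "one for children enrolled with" a first episode and the other for a prior episode. Under Sample Size it defines the target of 110 children per arm in each wheeze group (440 in all). Under Statistical Analysis it defines the two a-priori comparisons of azithromycin with placebo.

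**The concern.** A stratification rule has to give one answer for each child at the bedside, because the packet is drawn from the box it points to and that choice cannot be undone after dosing. Here the rule and its examples sit in one paragraph and give different answers for some children. If two research assistants, or the two hospitals, resolve the conflict differently, similar children enter different strata and count towards different enrolment targets. The two wheeze sub-groups would then not be the populations that the protocol says it wants to examine separately.

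**Working it through.** There is no stated figure to reproduce; the check is logical. I took 1 month as 30 days and 1 week as 7 days (the 30 days is my assumption) and applied the paragraph to children with no wheeze before the present episode.

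**Step 1: the literal clause.** Resolution means no respiratory symptoms, so a period without resolution is a symptomatic period. The clause therefore requires duration < 30 days and longest symptomatic run ≤ 7 days.

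**Step 2: the meaning that the examples point to.** Examples 2 and 3 depend on how long the child was free of symptoms. The matching rule is duration < 30 days and longest symptom-free gap ≤ 7 days.

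**Step 3: test children.**

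| Duration (days) | Longest symptom-free gap (days) | Longest symptomatic run (days) | Literal rule | Rule read as symptom-free time | Example that applies |
|---|---|---|---|---|---|
| 5 | 0 | 5 | first-time | first-time | none |
| 14, 20 or 29 | 0 | 14, 20 or 29 | not first-time | first-time | none |
| 20 | 10 | 5 | first-time | not first-time | none |
| 30 | 0 | 30 | not first-time | not first-time | Example 3: first-time |
| 30 | 7 | 12 | not first-time | not first-time | Example 2: repeat; Example 3: first-time |
| 30 | 8 | 11 | not first-time | not first-time | Example 2: repeat |
| 31 | 0 | 31 | not first-time | not first-time | Example 1: repeat |

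**Step 4: what the table shows.**

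- *Reversal.* The two readings disagree in both directions. Fourteen days of unbroken symptoms fail the literal rule (14 > 7) but pass the symptom-free reading (0 ≤ 7). A 10-day gap with short symptomatic runs passes the literal rule (5 ≤ 7) but fails the other (10 > 7).
- *Exactly one month.* The rule requires less than one month, so 30 days fails under either reading. Example 3 accepts one month, and Example 1 makes a child a repeat wheezer on duration only beyond one month.
- *Exactly one symptom-free week.* Example 2 counts a one-week gap as enough for repeat. Example 3 asks whether any gap was longer than one week; 7 > 7 is false, so the same child is first-time.

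The last two conflicts do not depend on how the double negative is read.

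**Step 5: size.** The protocol gives no distribution of symptom duration or symptom-free gaps at presentation. The share of children in the conflicting zones cannot be calculated.

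**The case against.** The strongest reply is that the double negative is a drafting slip which its own paragraph repairs. Examples 2 and 3 both speak of symptom-free time, and the protocol describes its research assistants as trained. The screening and patient data forms (Appendices D and F) and the detailed criteria (Appendix E) are not shown and may state the rule more clearly. The protocol says that the research assistant assigns the packet, but not exactly how wheeze history is established. It is also fair that Example 3 does not contradict the literal clause for every child it covers: a child with short gaps and no symptomatic run over a week meets the run condition. Finally, duration of illness is listed as a key baseline variable, so some onset information is probably collected.

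Most of this stands as a limit on the consequence. Staff who follow the examples would avoid the reversal. It does not clear the paragraph, because the examples disagree with each other at one symptom-free week and Example 3 disagrees with the rule at one month. Parents often answer in just these round units, so such children are plausible. The items listed under Baseline Assessment do not name a symptom-free gap, so those items alone would not allow the stratum to be checked later.

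A reader might go further and infer that first-ever episodes longer than a week will be sent systematically to the previous-wheeze box, diluting the contrast between the groups by a calculable amount. The protocol does not support that. It gives no misplacement rate and no expected difference in drug effect between the groups, the literal reading moves children both ways, and the stated comparisons are within each wheeze group.

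**Conclusion.** The paragraph is wrong as written and should be corrected. Its literal wording reverses the meaning of its second and third examples, and two boundary conflicts remain under the charitable reading. The consequence is inconsistent membership of the strata, the enrolment targets and the two sub-groups that the protocol describes as powered.

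The harm is bounded. A reader might infer that the main result is compromised; it is not. The stratum is set before allocation and children are randomised within whichever stratum they enter, so the overall azithromycin-placebo comparison is not biased by misclassification. Within each stratum as randomised the comparison is still randomised; what becomes unclear is which children it describes. Nor is wheeze history the only effect modifier examined, since Statistical Analysis also plans an interaction between drug and atypical bacterial infection.

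The contradiction and the one-week conflict rest on the text alone. The 30-day month matters only for putting numbers in the table. The number of children affected is unknown.

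**What to change.** Replace the definition with one mutually exclusive rule stated in terms of symptom-free time, and remove the double negative. For example: first-time means no wheeze before this episode, onset within a stated number of days, and no symptom-free interval at or above a stated number of days since onset; every other child is previous wheeze. The investigators should choose each limit once (30 and 7 days would be one choice), say which side of it the boundary value falls on, and rewrite all three examples to agree.

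Record the onset date and the longest symptom-free gap on the screening form, if they are not already there, so that the stratum can be verified.

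The cost is a one-paragraph wording change and at most two entries on the form, with no extra patients or procedures.

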#### 6. RESEARCH DESIGN

**Study Overview and Setting:** We propose a two arm, double blind, randomized placebo controlled trial conducted in two urban pediatric emergency departments (Alberta Children's Hospital (ACH), Calgary and Stollery Children's Hospital (SCH), Edmonton). (*Appendix A – Study Design Schema*)

**Patient recruitment:** Starting January, 2010, trained research assistants will be on-call 16 hours per day, seven days per week (*Appendix B – Emergency Medicine Research Associates Program*). The triage nurse will notify on-call research assistants about children 12-60 months of age who present with wheeze during the study period. Written, informed consent will be obtained as follows: 1) a video of a primary investigator explaining the study will be played for the parent (or legal guardian) by the assistants, 2) a primary investigator or senior research coordinator will be available by telephone to answer any questions the parent/legal guardian might have about the study 3) the research assistant will ask the parent/legal guardian who have verbally agreed to participate to sign the written consent form (*Appendix C – Consent Form*). A more lay description of the study including rationale, objectives and the study commitment will also be distributed as a brochure.

We propose to implement a lottery remuneration process within the ED. For each individual screened, the research assistant, admitting clerk, the nurse facilitating the enrollment visit can complete a ballot for entry. The ballot will contain the patient's bed number, time and date of the patient encounter. RA will check the handed ballot. The entry for RA will be confirmed through check box. The lottery draw will be completed after every 1000 entries. The winner will receive a Safeway Gift card for \$500.

**RMO Database:** We will maintain a database for eligible individuals who refuse, are missed, or are otherwise excluded to assess the generalizability of our study sample.

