***Safety monitoring committee and termination policy:*** Adverse events will be actively monitored up to 30 days after the last of Azithromycin was given (day 5). Any child who develops symptoms consistent with adverse effects to azithromycin as evidenced by diarrhea or loose stools, nausea, abdominal pain, and vomiting (common side effects), symptoms of allergic reaction (hives), changes in mood or behaviour, arrhythmia/tachycardia will result in the review of their case by a safety monitoring committee consisting of a pediatric pulmonologist, allergist, and general pediatrician. The committee will review the case and decide whether to break the code and/or terminate the study based on the particulars of the case. If upon review there are concerns about the patient, the code would be broken and the randomization drug discontinued. The panel may consider terminating the study if there are profound adverse effects that would reflect concerns for all children.

***Sample Size and Minimal Clinically Important Difference:*** The telithromycin in acute adult asthma study demonstrated a 50% reduction in asthma symptoms among those using telithromycin (16% asthma symptoms in the placebo group versus 8% in the telithromycin group). We have used this data to estimate the magnitude of effect for our sample size calculations (a 50% decrease in the number of days to symptom resolution). Enrolment of 110 children per treatment arm per first-time versus previous wheeze (total 440), using a one-way ANOVA, will provide 80% power to detect at the .05 level, a 1.18 day

differences in the two treatment groups. This calculation assumes a conservative standard deviation of 6 days in symptoms duration and a 10% loss to follow-up. For the planned sub-group analysis of first-time versus previous wheeze, we have sufficient power to detect a 1.36 day difference between the azithromycin and placebo groups (*Appendix M – Power Calculation*). We think that a reduction in the duration of symptoms by one day or more is likely to be considered meaningful because of its implication for a child missing daycare or school, or parents missing work.

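### The code-access sentence, as worded, gives both sites' research teams the master randomization code during the trial, probably through a missing 'not', and contradicts the double-blind design

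*Protocol*

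**What the plan says.** All of these statements are in Section 6 of the protocol.

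- **Randomization code access:** "The Research team from both sites will have access to the master randomization code until patient enrolment is completed". The sentence then adds a second condition that prolongs the access until the analysis plan is settled. This is the only paragraph devoted to who may see the code, and it carries no exception.
- **Study Overview and Setting:** the trial is a "two arm, double blind, randomized placebo controlled trial conducted in two urban pediatric emergency departments". Section 2 (Overall Aim) also calls it double-blind.
- **Blinding of azithromycin:** "The research assistant who assigns the intervention will be unaware of the next group assignment". The reason given is that "study drugs will be packaged identically and identified only by a sequential study number".
- **Randomization method:** "DDIC will produce the study packages, complete the block randomization, and number the bottles". The numbered packages, "in addition to the master code will be available to both study sites if de-blinding is required".
- **Safety monitoring committee and termination policy:** for a child with a suspected adverse effect, "The committee will review the case and decide whether to break the code and/or terminate the study", depending on the particulars of that case.

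**The concern.** A double-blind trial has to withhold the allocation list from recruiting and assessing staff while children are being enrolled and followed, and from whoever settles the analysis while choices are still open. The code-access sentence grants access for much of that period and sets its end at about the point when a blinded team would normally receive the code.

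Three safeguards would be at stake if a site acted on the sentence as written.

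- **Concealment at enrolment.** Research assistants obtain consent and hand out packets in numbered order. Anyone holding the list can read the next allocation from the packet number.
- **Outcome ascertainment.** The primary outcome is the time to symptom resolution in a diary scored by parents. Research assistants telephone those parents at 24 hours, 72 hours, 5 days and 14 days to ask about symptoms and recent diary entries. A site coordinator takes the history and examines the child at day 21.
- **Analysis choices.** The Statistical Analysis paragraph leaves several decisions to the data: transformation or Kruskal-Wallis depending on a normality test, covariate adjustment if baseline factors are imbalanced, and adjustment if co-interventions differ. The code-access sentence would keep the code available while those choices are made.

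**Working it through.** No arithmetic applies to the contradiction itself. The check is to set the statements side by side and ask whether they can all be true.

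| Place in Section 6 | Who may see the code | When |
|---|---|---|
| Randomization code access | Research team, both sites | Routinely, until enrolment ends and analysis decisions are final |
| Randomization method | Both sites | Only if unblinding is needed |
| Blinding of azithromycin | Not the assigning research assistant | At assignment |
| Safety monitoring | Code broken on the committee's decision | Case by case, after review |
| Study Overview | Double blind, so neither families nor study staff | Throughout |

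1. **Row 1 against row 2.** Routine access and access conditional on a need to unblind cannot both be the rule. Row 2 does not say that it limits row 1.
2. **Row 1 against row 3.** Concealment is said to rest on identical packaging and a sequential number. The master list is what turns that number into a treatment, so the packaging gives no protection against someone who holds the list. The two rows are compatible only if research assistants are outside the research team. The protocol neither defines the team nor excludes them.
3. **Row 1 against row 4.** A committee decision to break the code for one child has little meaning if the site already has the code.
4. **Row 1 against row 5.** Site staff with routine access to the list are not blinded.
5. **Does the sentence make sense with 'not' inserted?** Yes. Withholding the code until enrolment ends and analysis decisions are final is a normal blinding clause, and it agrees in direction with the other four rows. A grant of access that expires at that point has no evident purpose. A missing word is therefore the likeliest cause.
6. **Would 'not' alone be enough?** Not quite. The sentence names the end of enrolment but not the end of follow-up. The diary runs to day 21 and is extended for children whose symptoms have not resolved, a call follows at day 35, and chart review is at 6 months. If analysis decisions were settled early, the code could be released while the last children enrolled were still being assessed.

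**Size.** The document gives nothing from which to estimate how far knowledge of the allocation would shift parent-scored days. For context only, the sample-size paragraph states a detectable difference of 1.18 days with an assumed standard deviation of 6 days, which is 1.18 / 6 = 0.20 standard deviations. This shows that the target effect is small. It does not measure the bias.

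**The case against.** The strongest reply is that this is a typing error in a plan that is otherwise set up for blinding. An outside centre generates the list and numbers the bottles, the bags are sealed and opaque, drug and placebo are matched for look, smell and taste, the assigning assistant is said to be unaware, and code breaks go to a committee. That reply is probably right about the cause, and it rules out reading the sentence as a deliberate decision to run the trial unblinded. It does not remove the defect. This is the operative rule on code custody, a site that followed it would be complying with the protocol, and no other paragraph overrides it.

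The reply also stands against several stronger readings that a reader might infer:

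- **That one emergency would open every allocation.** The randomization-method paragraph does not describe how a code break is carried out, and the safety paragraph describes review of individual cases. The wording is loose because it names the master code, but it does not say that the whole list is opened.
- **That the site teams make the analysis decisions.** Neither the code-access sentence nor the Statistical Analysis paragraph says who makes them.
- **That all 440 planned allocations are exposed.** Permitted access is not actual exposure, the research team is undefined, and the assigning assistant is said to be unaware.
- **That staff check the primary outcome.** The coordinator's stated verification covers the medication diary. Parents score the symptoms and are not given the code, and the telephone record of diary data is a back-up. Staff influence on the outcome is possible but indirect.

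**Conclusion.** The point holds as an internal contradiction in an operative rule. Read literally, the code-access sentence would defeat allocation concealment and staff blinding, and it conflicts with the double-blind design, the unaware assistant and the conditional access elsewhere in Section 6. The probable cause is a dropped negative. That reading is an inference from the surrounding text, because the document does not confirm it.

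The consequence is conditional: bias in selection, ascertainment or analysis choice could arise only if the sentence were acted on, and its size cannot be derived from the protocol. The document does not support a claim that the trial was in fact unblinded. The correction is still necessary before the protocol is relied on, because concealment and blinding underpin the treatment comparison and the fix costs almost nothing.

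**What to change.** 1. **Randomization code access.** Reword to say that the research team at both sites will not have access to the master code until enrolment and follow-up are complete and all analysis decisions are final. State that the code is held by DDIC or another party outside the research team.
2. **Randomization method.** Replace the phrase that makes the master code available to the sites with a statement that, where unblinding is required, only the individual child's allocation is revealed.
3. **Safety monitoring.** Cross-refer the two paragraphs so that the case-by-case code break and the unblinding provision describe the same process.

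The cost is a short wording amendment and an arrangement for single-child code breaks. DDIC already generates the list and numbers the bottles, so no change to sample size, visits or data collection is needed. The mechanics of a code break, such as its form and logging, can sit in operational documents.
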